### LN products and distribution

LifeNet® LN is a net with deltamethrin-incorporated into 100 denier polypropylene filaments at 8.5 g AI/kg or 340 mg/m^2^ (Bayer CropScience, Germany) [26]. It has undergone a WHO generic risk assessment model and does not pose undue hazards to the user when used as instructed [34]. LifeNet® LN has attained a WHO interim recommendation following successful Phase II experimental hut trials in 2011 [26] and will be granted a full WHO recommendation following successful completion of a Phase III evaluation.

Under WHOPES guidelines, LifeNet® LN efficacy and durability will be compared to a LN which has already completed Phase III evaluations successfully. PermaNet® 2.0 LN (Vestergaard Franden, Switzerland) is a multifilament polyester net treated with deltamethrin to a target concentration of 55 mg/m^2^, bound in a wash-resistant resin coating that received full recommendation in 2008 and is widely used by NMCPs [35]. Because LifeNet® LN introduces a novel polymer to the range of textile materials currently favoured for nets it is important to test the polypropylene LN against net products representative of different material types. In addition to a polyester LN typified by PermaNet® 2.0 LN, LifeNet® LN will be compared with a net brand submitted to WHOPES, made from polyethylene monofilaments incorporated with deltamethrin to a target concentration of 63 mg/m^2^ (Table 2). This study will provide a unique opportunity to evaluate the relative durability and residual efficacy of three LNs each made from different textiles, containing the same insecticide (deltamethrin), following two different treatment methods (incorporation and coating).

**Table 2 Tab2:** Characteristics of three LN brands distributed in the study

LLIN Brand	Manufacturer	Fabric	Deltamethrin Concentration	A.I. Application	Denier	Av. Mesh Size Per cm^2^	Bursting Strength (kPa)	Colour	Size (cm)	WHOPES Recommendation	References
LifeNet®	Bayer CropScience, Germany	Polypropylene	340 mg/m^2^	Incorporated into fibres	100	21–29	450	White	W190 × L180 × H 150	Interim (2011)	[26]
PermaNet® 2.0	Vestergaard Frandsen, Switzerland	Polyester	55 mg/m^2^	Resin coating	100	24	250–350	Blue	W190 × L180 × H 150	Full (2008)	[35]
Polyethylene LN	Bestnet A/C, Denmark	Polyethylene	63 mg/m^2^	Incorporated into fibres	110	21	540	White	W190 × L180 × H 150	Withdrawn (2014)	[46]

LNs will be distributed using a voucher scheme; study team members will visit participating households door-to-door and distribute coupons which specify the type and number of nets to be received from a focal point in each hamlet. At the time of LN distribution, householders will be asked to begin using their nets immediately, to store and not use any existing nets and reminded about appropriate use and maintenance of their nets; storage of existing nets will be verified by house visits 1 month post LN distribution. Study teams will also offer assistance to erect nets over sleeping areas. Participants will be advised to report any adverse effects, including headache, numbness, itching, sneezing, nasal discharge, discharge from eyes, nausea and unpleasant smells, and to seek medical care from the nearest health facility if the symptoms persist or if they observe any signs of malaria or other vector-borne diseases. Study teams will offer assistance and reiterate this information every time a LN is withdrawn for laboratory analysis and replaced throughout the monitoring period.

### Cross-sectional surveys: bioefficacy

To determine the insecticidal efficacy of each intervention, at the beginning of the study (t0) and every 6 months thereafter (t6, 12, 18, 24, 30), 30 LNs of each brand will be randomly selected from the net master list and assessed using standard WHO cone bioassays [8]; 50 LNs of each brand will be drawn randomly for the survey at 36 months (t36). LNs will be removed from participating households and replaced with new nets of the same type.

From each LN, five samples (25 × 25 cm) will be cut at positions 1 to 5 (Fig. 3). All bioassays will be performed using 2–5 day old non-blood fed, laboratory-reared susceptible *An. gambiae s.s.* Kisumu strain. Twenty mosquitoes will be exposed to each netting sample, in four standard WHO cones fixed with a plastic manifold, for 3 min and then held for 24 h in paper cups with cotton wool soaked with 10% sugar solution; knock-down will be recorded after 60 min and mortality after 24 h. Mosquitoes exposed to an untreated net will be used as a negative control in each round of assays. All bioassays will be performed at 25 ± 2 °C and 75 ± 10% relative humidity.

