**Methods:**

This is a prospective three-arm household randomized, equivalence trial of LNs in Tanzania, with nets as the unit of observation. Equal numbers of houses will be randomized to receive deltamethrin-treated polypropylene, polyester or polyethylene LNs; all sleeping spaces in a given household will be provided with one type of net. Bioefficacy (insecticidal activity against mosquitoes), insecticide content of net fibres, and fabric integrity (number, location and size of holes) will be measured every 6 months, using WHO cone or tunnel bioassays, chemical analysis and calculation of hole index, respectively. A cohort of LNs will be surveyed annually to assess survivorship (median LN survival time) and cumulative loss of fabric integrity. Field durability outcomes will be compared with laboratory strength tests.

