### Study design, randomization, blinding and bias

This will be a prospective cluster randomized controlled, equivalence trial with nets as the unit of observation. Following household enumeration, global positioning system (GPS) coordinates will be recorded and baseline socio-demographic and economic data, including age, sex, occupation, education, household wealth, sleeping habits and number of spaces, ownership and use of other mosquito nets and net preferences (size, colour, shape and washing habits) will be collected using a standardized questionnaire.

Once baseline chemical analysis of LNs is completed and confirmed to be within WHO specifications, the nets will be distributed. The monitoring period will be 3 years, beginning August 2014 (Table 1). At study onset, equal numbers of households from eighteen hamlets will be randomized to the three study arms. All participating households in a specific hamlet will be provided with the same type of LN to achieve universal coverage, assuming an average of 4.0 sleepers and 2.1 sleeping places per household. To ensure all members in a participating household are using the same LN brand, any existing nets will be removed and replaced by study LNs. All LNs will be issued free of charge to recipients. Net users will be encouraged to retain the LNs they are given and not to sell or exchange them with other study participants. If for any reason an owner stops using a net, they are requested to volunteer the reason and to store the net for later inspection by investigators.

**Table 1 Tab1:** Timetable of study activities

Activity	Pre-Intervention	Post Intervention monitoring period (months)						
		0	6	12	18	24	30	36
Community selection, sensitization and consent	X							
Baseline census and household survey	X							
LLIN distribution	X							
Cross-sectional surveys: bioefficacy assays	X	X	X	X	X	X	X	X
Cross-sectional surveys: chemical assays	X			X		X		X
Cross-sectional surveys: fabric integrity		X	X	X	X	X	X	X
Cross-sectional surveys: fabric strength		X	X	X	X	X	X	X
Cross-sectional surveys: community practices		X	X	X	X	X	X	X
Cohort surveys: household survivorship and fabric integrity		X	X	X		X		X
Insecticide resistance monitoring	X			X		X		X
Adverse events monitoring		X						

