### Cross-sectional surveys: fabric integrity

At t6, 12 and 18 months post LN distribution, the 30 LNs destructively sampled for bioassays will be scored for physical integrity by draping the nets over a frame and counting the number and types (due to burning, tearing, split seams or animal damage) of holes of different sizes according to location on the net (top, upper side, lower side). Holes greater than 0.5 cm will be classified into the following categories: smaller than a thumb (0.5–2 cm); larger than a thumb but smaller than a fist (2–10 cm); larger than a fist but smaller than a head (10–25 cm) and larger than a head (>25 cm). At t24 and 36, physical integrity of the nets will be evaluated for a randomly selected sample of 100 LNs of each brand (including the 30 destructively sampled for bioassays). Net integrity (hole index, hole area and circumference) of each net type will be calculated as per WHO guidelines [28] (Table 3). In addition, any evidence of repairs and types of modification will be recorded.

**Table 3 Tab3:** LN hole size index

Hole Size Categories (cm)	Hole Diameter^a^ (*d;* cm)	Hole radius (*r* = *d/*2)	Hole Area^b^ (π**r* ^2^)	Hole Index^c^
0.5–2.0	1.25	0.625	1.23	1
2–10	6	3	28.28	23
10–25	17.5	8.75	240.56	196
>25	30	15	706.95	576

^a^Weights for each size category were estimated assuming that the average hole diameter was the midpoint in each category, except for the largest hole where the average diameter was assumed to be 30 cm

^b^The approximate area of an average sized hole from each category was estimated by assuming each hole was approximately circular

^c^Final weights for each size category were then estimated by dividing the area encompassed by a hole in the smallest size category (i.e. 1.23)

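### The survey draws are not stated to be stratified by hamlet, although net type is supplied by hamlet; a proportional draw within hamlet would gain a little precision at almost no cost

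*Protocol article*

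**What the plan says.** **The draw.** Under *Cross-sectional surveys: bioefficacy*, the rule for every round before month 36 is this: "30 LNs of each brand will be randomly selected from the net master list". For month 36 the number rises to 50 per brand. The section on fabric integrity adds, for its surveys at two and three years, that "physical integrity of the nets will be evaluated for a randomly selected sample of 100 LNs of each brand". Two restrictions appear elsewhere: one net per household (*Sample size rationale*) and no sampling of cohort households (*Cohort study*). No stratum or quota by hamlet is stated.

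**The allocation.** The section *Study design, randomization, blinding and bias* calls the trial cluster randomized and takes the households, in equal numbers per arm, from eighteen hamlets. On supply its rule is: "All participating households in a specific hamlet will be provided with the same type of LN to achieve universal coverage". The Abstract's Methods paragraph points the other way: "Equal numbers of houses will be randomized to receive deltamethrin-treated polypropylene, polyester or polyethylene LNs".

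**The sampling frame.** The same design section describes a nine-digit net ID that contains the village, hamlet, household and net numbers.

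**The concern.** If net type follows the hamlet, the nets of one brand come from a handful of hamlets that may differ in housing, washing habits and wear. A draw that takes no account of hamlet leaves the share of each hamlet to chance. That share then differs between brands at one survey, and within a brand from one survey to the next.

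This adds noise to between-brand comparisons and to trends such as the average rate of insecticide loss, which *Data analysis* estimates from repeated surveys. The information needed to remove that noise is already in the net ID. Precision is at stake, not bias.

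**Working it through.** **1. The plan's own figure.** *Sample size rationale* gives a minimum of 320 households per arm. Five rounds of 30, one of 50, and three years of 20% attrition added up give (5 × 30 + 50) × (1 + 3 × 0.20) = 200 × 1.6 = 320. The figure reproduces if the month 0 round is left out. I use 320 as the sampling frame per arm.

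**2. Assumptions not in the documents.** Six hamlets per arm (18 / 3), an ICC (ρ) of 0.02 to 0.2, and equal hamlet sizes unless stated otherwise. Total variance is scaled to 1. Shrinkage of the frame between surveys is ignored.

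**3. How uneven is the draw?** With 30 nets, each hamlet expects 30 / 6 = 5. The SD is √(30 × 1/6 × 5/6 × 290/319) = 1.95. Some hamlet supplies two nets or fewer in 48% of draws. A hamlet is missed altogether in 1.9% of draws at n = 30 and 0.03% at n = 50. These figures depend on hamlet size: with assumed sizes of 80/70/60/50/35/25 households, a hamlet is missed in 10.8% and 1.4% of draws.

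**4. Variance of one survey mean for an arm**
- Unstratified: (1 − ρ)/n + ρ[1/6 + (5/6)/n × f], with f = (320 − n)/319
- Proportional within hamlet: (1 − ρ)/n + ρ/6

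Example, n = 30 and ρ = 0.2: f = 290/319 = 0.909. Unstratified: 0.8/30 + 0.2 × (0.1667 + 0.0253) = 0.0651. Proportional: 0.8/30 + 0.2/6 = 0.0600. The ratio is 0.922, a cut of 7.8%.

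**5. Change between two surveys.** If each hamlet's effect is the same at both surveys, the ρ/6 term cancels. The ratio becomes [(1 − ρ)/n] / [(1 − ρ)/n + ρ(5/6)/n × f]. Example, n = 30 and ρ = 0.2: 0.02667 / (0.02667 + 0.00505) = 0.841, a cut of 15.9%.

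| n | ρ | Cut in variance, one survey | Cut in SE, one survey | Cut in variance, change |
|---|---|---|---|---|
| 30 | 0.02 | 1.4% | 0.7% | 1.5% |
| 30 | 0.05 | 3.1% | 1.5% | 3.8% |
| 30 | 0.10 | 5.1% | 2.6% | 7.8% |
| 30 | 0.20 | 7.8% | 4.0% | 15.9% |
| 50 | 0.05 | 2.5% | 1.3% | 3.6% |
| 50 | 0.20 | 5.4% | 2.7% | 15.0% |

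With 100 nets the single-survey cut is smaller, 0.9% at ρ = 0.02 and 2.7% at ρ = 0.2. With unequal hamlets (assumed shares 30/22/18/14/10/6%) and n = 30, the cuts are 1.3–6.7% for one survey and 1.5–15.3% for change.

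**6. Effect on the month 36 criterion.** For an 80% pass rate with n = 50, the 95% half-width is 1.96 × √(0.16 × variance). It moves from 13.1 to 13.0 percentage points at ρ = 0.05 and from 17.9 to 17.4 at ρ = 0.2. Ignoring clustering would give 11.1. The gap between 11.1 and 13.0 or 17.4 comes from having only six hamlets per arm, and stratifying does not close it.

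**7. Equal numbers per hamlet.** Take the unequal shares above, with Σw² = 0.204. Five nets per hamlet, weighted back to the product percentage, give variance ρ × 0.204 + (1 − ρ) × 0.204/5. At ρ = 0.02 this is 0.0441 against 0.0372 for the present draw, 18% more. At ρ = 0.2 it is 0.0734 against 0.0723, about 2% more.

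**8. If households were randomized.** Each brand could be spread over all 18 hamlets. Stratifying then removes ρ(17/18)/n from each arm's contribution to the between-brand variance, beside (1 − ρ)/n. The cut is 0.0189/(0.98 + 0.0189) = 1.9% at ρ = 0.02 and 0.1889/(0.8 + 0.1889) = 19% at ρ = 0.2, leaving out the finite-population factor. This is an upper figure, because 30 nets over 18 hamlets (1.7 each) cannot match the proportions exactly.

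**The case against.** A random draw from the full list is valid and unbiased. The protocol makes the net the unit of observation and judges the product on the share of sampled nets that pass. For that quantity the gain is at most 4% of a standard error at n = 30, and no decision would plausibly turn on it. The article says only that nets are selected at random. It does not call the draw simple, it already states one net per household and the exclusion of cohort households, and a full protocol may specify more. Hamlet sizes and the ICC are not given, and the gain for change assumes stable hamlet effects. Durability trends also have the longitudinal cohort, which this draw does not touch.

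All of this stands, and it limits the size of the point. It does not remove it: the proportional draw lost precision in no case computed, and its cost is trivial.

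Two stronger readings are tempting:
- **Hamlets will often go unrepresented.** The documents give no hamlet sizes. With equal sizes a miss is uncommon at 30 nets and very rare at 50; high figures come only from assumed unequal sizes.
- **Much larger precision gains are available by sampling equal numbers per hamlet.** Such gains belong to an equally weighted mean of hamlet means, which the protocol does not use. For the product-level percentage, equal numbers lose precision if hamlets differ in size (step 7).

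**Conclusion.** The point holds as a low-severity design improvement. No stratification by hamlet is stated for draws of 30, 50 or 100 nets per brand, although the design section supplies net type by hamlet and every net ID identifies the hamlet. The cost is a small loss of precision: at n = 30, about 1–8% of the variance of a single survey mean and about 1.5–16% of the variance of change between surveys. These ranges rest on six hamlets per arm and an ICC of 0.02 to 0.2; the second also needs hamlet effects that are stable over time.

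The documents do not support calling the draw biased or invalid, and they do not show that stratifying would repair the precision lost through the small number of hamlets. The conflict between household and hamlet allocation is a separate matter to settle, but the proportional draw helps under either.

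**What to change.** - **Draw.** In the bioefficacy and fabric-integrity sections, state that for the remaining surveys, including month 36, nets of each brand are drawn at random within hamlet in proportion to that brand's eligible nets there. Keep one net per household and the exclusion of cohort households. Where numbers do not divide evenly (50 or 100 over six hamlets, or 30 over 18), a systematic draw from a random start on the list sorted by hamlet does this.
- **No equal quotas.** Do not fix equal numbers per hamlet. The proportional draw needs no weights and leaves the 80% criterion unchanged.
- **Analysis.** Include hamlet as a cluster if net type was allocated by hamlet, or as a stratum if it was allocated by household.
- **Reconcile** the Abstract and the design section on the unit of allocation.
- If the full protocol already stratifies the draw, one sentence saying so is enough.

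**Cost:** one sentence and a few lines of code on the existing master list; no extra nets, visits or assays. The article reports the trial in monitoring year 2, so earlier draws stay as they are and later ones can still be changed.

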**Fig. 3 Fig3:**
[figure not shown]
Sampling scheme for LNs

Bioassay data for position 1 will be analysed separately from the others (2–5) considering this part of the LN is subjected to excessive abrasion during routine use; this portion of net is frequently manipulated while tucking the LN under the bed/mattress. Likewise, no chemical analysis will be conducted on position 1 samples. If there are significant variations between bioassay results, mean results of positions 2–5 will only be used.

If LNs do not meet the efficacy criteria of ≥95% knock-down rate after 60 min or mortality of ≥80% after 24 h in the cone bioassays, they will be subjected to a tunnel test using a guinea pig as bait to determine whether they meet the efficacy criteria of ≥80% mortality or ≥90% blood feeding inhibition [28]. The LN piece will be attached to a disposable cardboard frame, placed at one third of the length of a glass tunnel measuring 25 cm^2^ × 60 cm, exposing 400 cm^2^ (20 × 20 cm) of surface netting. Nine holes, each 1 cm in diameter (one in the centre of the square and the other eight equidistant at 5 cm from the border) will be made in the netting to allow for passage of mosquitoes; a netting-covered cage is attached at each end of the tunnel to introduce mosquitoes. In the shorter section of the tunnel, a guinea pig will be restrained and one hundred 5–8 day old non-blood fed *An. gambiae s.s.* Kisumu mosquitoes will be introduced from a cage positioned at the longer end of the tunnel. The experiment will begin at 18:00 and end at 09:00 the following morning, after which mosquitoes will be scored according to whether they passed through the netting, whether they successfully blood fed and whether they survived the exposure period. The test will be replicated twice with 50 mosquitoes per test using the piece of netting from the failed LN that gave a cone mortality result closest to the average obtained for positions 2–5. All tunnel tests will be performed at 25 ± 2 °C and 75 ± 10% relative humidity under subdued light. A tunnel with untreated netting will be used as a negative control. Because blood-feeding rate in the negative control influences contact and mortality with the pyrethroid-treated samples, a minimum blood-feeding rate of 50% in the controls is required in the paired treatment-control tunnel tests.

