### Data analysis

All statistical analyses will be performed using STATA version 13 (StataCorp LP, College Station, TX, USA).

Bioefficacy data from the WHO cone tests will be used to calculate proportional knock-down and mortality. Bioefficacy results from the netting pieces of each LN will be pooled to determine whether the net meets the WHO efficacy criteria of ≥80% mortality or ≥95% knockdown. Bioefficacy data from the WHO tunnel tests will be used to determine whether nets that fail the cone test meet the WHO efficacy criteria of ≥80% mortality or ≥90% blood-feeding inhibition. Blood-feeding inhibition will be assessed by comparing the proportion of blood fed females (alive or dead) in treated and control tunnels. Overall mortality will be measured by pooling the immediate and delayed (24 h) mortalities of mosquitoes from the two sections of the tunnel, relative to the control. Mortality data in both WHO cone and tunnel tests will be corrected for negative control mortality using Abbott’s formula.

A candidate LN product must achieve the WHO requirement of at least 80% of sample nets meeting the bioefficacy criteria in the WHO cone bioassays or tunnel tests after 3 years of use.

Chemical analysis results will measure the mean (and standard deviation) target deltamethrin concentration in each type of LN to assist interpretation of the bioefficacy data. Insecticide content reported at each survey time will be used to estimate the average rate of insecticide loss from the original loading dose.

LN survivorship will be measured at each timepoint as the total number of each LN present in surveyed households (and used for sleeping under) divided by the total number of each LN originally distributed to households and not given away at each time point [6]. Median LN survival is the time point at which the estimate of functional LN survival reaches 50%. LN attrition is derived from the total number of LNs missing from each household (classified into categories of nets that have been destroyed or disposed for reasons other than poor fabric integrity, nets used for other purposes and nets destroyed for reasons of poor fabric integrity) divided by the total number of each LN distributed to households. LNs retained for inspection but no longer used for reasons of poor integrity will be included among the nets lost to attrition.

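### The protocol gives conflicting rules, one of them data-dependent, on whether position 1 counts towards a net's cone-test verdict

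*Protocol article*

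**What the plan says.** The protocol article, *Cross-sectional surveys: bioefficacy*, sets out the sampling: "From each LN, five samples (25 × 25 cm) will be cut at positions 1 to 5". Each piece is tested with the same number of insects: "Twenty mosquitoes will be exposed to each netting sample, in four standard WHO cones fixed with a plastic manifold".

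Three statements then bear on position 1.

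- The text after Fig. 3 in that section separates it without condition, because tucking the net in abrades that area: "Bioassay data for position 1 will be analysed separately from the others (2–5".
- Shortly afterwards the same text makes the choice of pieces conditional: "If there are significant variations between bioassay results, mean results of positions 2–5 will only be used". This implies that position 1 is used otherwise. No test, level, endpoint or unit (net, brand or survey) is given.
- *Data analysis*, where the net-level verdict is defined, says: "Bioefficacy results from the netting pieces of each LN will be pooled to determine whether the net meets the WHO efficacy criteria". Position 1 is not excepted.

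Two other provisions leave position 1 out without condition. No chemical analysis is done on it, and the tunnel-test piece is the one with the "cone mortality result closest to the average obtained for positions 2–5".

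The cone verdict opens the route to the second test: "If LNs do not meet the efficacy criteria of ≥95% knock-down rate after 60 min or mortality of ≥80% after 24 h", then "they will be subjected to a tunnel test using a guinea pig as bait". A product needs at least 80% of sampled nets to pass on either test after 3 years. With 50 nets per brand at 36 months, that is 40 nets.

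**The concern.** The set of pieces that defines the outcome should be fixed before the data are seen. Here one sentence lets the observed variation decide it, and the other two statements give different fixed answers. No passage says which prevails.

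The protocol itself expects position 1 to be more abraded, so the readings may well diverge in practice. If they do, cone pass rates for the three brands, or for successive surveys, may not rest on the same pieces. Which nets are sent to the tunnel test changes too, and a choice is left open at the 36-month analysis.

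**Working it through.** The protocol gives no figure on this point, so there is nothing to reproduce. The check is how far the readings can diverge on the mortality criterion.

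**Inputs from the protocol.** Five pieces with 20 mosquitoes each: 80 at positions 2–5, 20 at position 1, 100 in all. The mortality threshold is 80%, that is, at least 64/80 on positions 2–5 or 80/100 on all five.

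**Assumptions, not in the protocol.** The true mortality at each position, independent binomial counts, and, for the conditional rule only, a test run net by net at the 5% level.

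**Step 1: when the two fixed readings disagree.** Let m be mortality at positions 2–5 and q mortality at position 1. The five-piece mean is (4m + q)/5. A net that passes on positions 2–5 fails on all five when q < 4 − 4m:

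- m = 82.5%: q below 70%
- m = 85%: q below 60%
- m = 90%: q below 40%

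**Step 2: single nets.**

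- 66/80 = 82.5% (meets). Adding 13/20 gives 79/100 = 79% (misses). Fisher's exact p for position 1 against positions 2–5 is 0.12, so a 5% test would keep position 1 and the net would miss the mortality criterion.
- The reverse also occurs: 62/80 = 77.5% (misses), but adding 18/20 gives 80/100 (meets).

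**Step 3: probabilities by exact binomial enumeration.** For each pair of true rates, sum the probabilities of all outcomes with at least 64/80, or at least 80/100, dead.

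| True mortality, 2–5 / position 1 | P(meets), 2–5 | P(meets), all five | Meets on 2–5 but misses on all five |
|---|---|---|---|
| 85% / 70% | 0.916 | 0.750 | 17% |
| 85% / 60% | 0.916 | 0.560 | 36% |
| 85% / 50% | 0.916 | 0.357 | 56% |
| 90% / 70% | 0.998 | 0.968 | 3% |

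**Step 4: the conditional rule, if it were applied per net at 5%.** With positions 2–5 at 85%, Fisher's test would exclude position 1 in about 31%, 63% and 87% of nets as position 1 falls from 70% to 60% to 50%. A five-position chi-square test (simulated) would do so in about 18%, 46% and 73%, so the choice of test also matters. Under the Fisher version P(meets) is 0.835, 0.836 and 0.879. A worse position 1 is discarded more often, so the chance of meeting the criterion does not fall and ends higher.

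**Step 5: from cone to final verdict.** A net that misses 80% mortality still passes the cone test on 95% knock-down. If it misses that too, it can pass in the tunnel. Take the 85%/60% row, ignore knock-down, and let a share r of cone failures pass the tunnel. The final pass rate is p + (1 − p)r:

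- r = 50%: 0.916 + 0.084 × 0.5 = 0.96 on positions 2–5; 0.560 + 0.440 × 0.5 = 0.78 on all five
- r = 70%: 0.916 + 0.084 × 0.7 = 0.97; 0.560 + 0.440 × 0.7 = 0.87

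The protocol gives no value for r.

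**The case against.** The strongest defence is that the bioefficacy text is a single sequence: look at position 1 apart, and if it differs use positions 2–5. The data analysis section does not literally say all five pieces and could mean whichever pieces are retained. Chemical sampling and the choice of tunnel piece already favour positions 2–5. On this view only one sentence is unclear, and how the check is run is detail for a fuller document.

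That reading is possible, but it leaves the data-dependent rule in place. It also needs the data analysis sentence to carry an exception that it does not state, after a section that has five pieces tested. The article does more than omit a detail: it states rules that conflict.

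Other parts of the defence stand:

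- **The net-by-net test is an assumption.** If the check were made per survey, 30 to 50 nets would give 600 to 1,000 mosquitoes at position 1 per brand. Low power would then hardly matter, and inclusion would not switch from net to net.
- **The effect is large only near the threshold.** With positions 2–5 at 90% and position 1 at 70% it is about three percentage points.
- **A mortality miss is not a product-level failure.** Knock-down and the tunnel test can both rescue the net, and the tunnel piece is chosen by reference to positions 2–5.

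A reader might also infer that the rule would act differently by brand, because coated and incorporated nets wear differently at the tucked edge. The protocol describes the two treatment methods and the abrasion, but does not say that loss at position 1 differs between them.

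**Conclusion.** The inconsistency is real and should be corrected. Two fixed rules and one data-dependent rule coexist for the pieces that make up the net-level cone verdict.

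On the mortality criterion, the choice between positions 2–5 and all five moves the chance of meeting it from 0.92 to 0.75 or 0.56 if true mortality is 85% at positions 2–5 and 70% or 60% at position 1. It moves it only from 0.998 to 0.968 at 90% and 70%. These mortalities are assumed; the protocol gives none by position. The exclusion rates of 31% and 63% also assume a Fisher test per net at 5%.

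What is affected is the cone pass rate and the selection of nets for the tunnel test. A reader might infer that the choice carries a product across the 80%-of-nets requirement. The documents do not support that. The requirement counts a pass on either test, while the rates above are for cone mortality alone, and the outcome turns on knock-down and tunnel results for which no figures are given. The final verdict changes only for nets that also miss 95% knock-down and then fail the tunnel test.

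**What to change.** Delete the conditional sentence in *Cross-sectional surveys: bioefficacy*. State there and in *Data analysis* that the cone verdict, for knock-down and mortality alike, uses the pooled result of positions 2–5 for every net, brand and survey. Report position 1 separately, and give the pass rate on all five positions as a sensitivity analysis.

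Positions 2–5 are suggested because they match the protocol's own chemical sampling and tunnel-piece choice. The essential change is one rule that does not depend on the data.

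The cost is a sentence in each of two sections and no new data, since all five pieces are tested anyway. The article puts the trial in monitoring year 2, so the rule could be settled before the 36-month survey. The downside is that the main rate leaves out the most abraded area, so the five-position rate should stand beside it.
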